#### AF burden

AF burden will be quantified by twice daily and symptom-triggered (onset and termination) Kardia recordings which will be sent daily. The time of the recorded AF event will be taken as the onset of the episode, with the next recorded sinus rhythm taken as the offset.

#### Changes in CMR

CMR will be performed by using 1.5-T scanner (MAGNETOM Verio, Siemens, Erlangen, Germany) of QEHB. ECG R-wave-gated, steady-state-free precession imaging (SSFP) [True-FISP] cine images of the left and right ventricle in vertical long axis, horizontal long axis, and serial contiguous short axis will be acquired, throughout the atria and ventricles according to standard parameters. Epicardial adiposity (EpAT) will be measured from atrioventricular (AV) grove to apex during ventricular end systole in short-axis stack images by contouring of each slide. The total volume will then be calculated by adding each slide. Late gadolinium images of the left atrium will be taken 15 min following intravenous gadolinium administration (0.1 mmol/kg). These images will be used to render scar images in an open-sourced CEMRGAPP to calculate left atrial fibrosis. The method of rendering has been published by CEMRGAPP group elsewhere [28]. Both clinical and research scans will be reported by an experienced imaging cardiologist ([name]).

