## Methods and design

### Study design and population

This is an open-label, uncontrolled, prospective, single-centre feasibility study of liraglutide in the treatment of obese AF patients injected for at least 13 weeks before and 52 weeks after AF ablation. Patients waiting for first-time AF ablation in QEHB will be invited for the study. We aim to recruit 30 patients who meet the eligibility criteria. Potential participants will be screened through cardiology outpatient clinics and the waiting list for AF ablation at QEHB.

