#### Inclusion criteria

Adult patients with paroxysmal or persistent AF (> 18 years of age)Symptomatic: Defined as palpitations, shortness of breath, and feeling of an irregular pulse or pause in heart activity, despite guideline-directed medical therapy (or inability to take medications)Body mass index above 30 kg/m^2^ (Mosteller equation)

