#### Electroanatomic mapping in the right atrium

Electroanatomic mapping of the right atrium will be performed at baseline before treatment and then restudied at the time of ablation to allow comparisons of datasets. The reason for choosing right atrial mapping over the left atrium is to reduce the risks involved in crossing the atrial septum in study participants. In our study, right atrial bipolar voltage will be measured using a high-density mapping catheter (HD-Grid, Abbott) at baseline, and bi-atrial mapping will be performed at the time of ablation. The RA mapping will be performed by an experienced electrophysiologist ([name]).

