### Statistical analysis

Descriptive statistics will be used to summarize demographics and medical histories. The number of patients recruited over 52 weeks will be reported as a percentage of those eligible. The adherence to the medication will be reported as a proportion of patients who tolerate a total cumulative dose of 657 mg of liraglutide or more over 52-week follow-up period. The cumulative dose of liraglutide will be calculated for each participant, and mean and standard deviation for all participants will be reported. The percentage of change in weight from baseline to the end of follow-up will be calculated for each participant, and the proportion of participants who lost weight ≥ 5% and < 5% will be reported. 

For the secondary outcome measures, descriptive statistics according to the data type will be used to report at each predefined time point (baseline, before ablation, and end of follow-up). Paired *t*-test will be used to compare the changes for continuous variables such as changes in CMR measurements, biomarkers, and electroanatomic data to determine potential mechanistic changes in relation to weight loss. As this is a feasibility study, the analysis will be reported as point estimates and corresponding 95% confidence intervals to provide precision of estimates, and no *p*-values will be reported. A Kaplan–Meier curve will be constructed for time to recurrence of AF at 1 year following ablation. This will be performed in preparation for the calculation of sample size with appropriate power for the future clinical trial based on a time-to-event superiority analysis.

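### The paired CMR and right atrial mapping changes are not stated to be read masked to visit, and no common rhythm is set for the two maps, so a reading or rhythm artefact could pass as a weight-loss effect

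*Protocol article*

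**What the plan says.** All references are to the protocol article.

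- **Design.** Study design and population: "This is an open-label, uncontrolled, prospective, single-centre feasibility study of liraglutide". There is no comparison group.
- **CMR.** Under Changes in CMR, cine images are acquired as "ECG R-wave-gated, steady-state-free precession imaging (SSFP) [True-FISP] cine images". Epicardial fat is measured "during ventricular end systole in short-axis stack images by contouring of each slide", and the slices are then summed. Left atrial scar is rendered in software from late gadolinium images. On the reader, the section says: "Both clinical and research scans will be reported by an experienced imaging cardiologist". It says nothing on masking to date, visit or scan order.
- **Mapping.** Under Electroanatomic mapping in the right atrium, the study is "performed at baseline before treatment and then restudied at the time of ablation to allow comparisons of datasets". The baseline study covers the right atrium only; the study at ablation covers both atria. On the operator: "The RA mapping will be performed by an experienced electrophysiologist". No rhythm or pacing condition is given for either occasion.
- **Population.** Inclusion criteria: "Adult patients with paroxysmal or persistent AF".
- **Analysis.** Statistical analysis: "Paired *t*-test will be used to compare the changes for continuous variables", with the stated purpose of finding possible mechanistic changes linked to weight loss. Results are given as estimates with 95% confidence intervals and without p-values. No stratification or restriction by rhythm is mentioned.
- **Status.** The Abstract and the Aims call these outcomes exploratory. They also appear under the secondary outcome measures. The feasibility criteria do not use them.

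**The concern.** With no control arm, the within-patient change is the only evidence the study will have on mechanism. Anything that differs systematically between the two visits goes straight into that change. Two such sources are left open.

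1. **Reading.** Contouring fat slice by slice and rendering scar both involve judgement. A reader who knows which scan follows treatment, and expects improvement, can shift the difference without intending to. For mapping, the operator necessarily knows the visit, because the second study is bi-atrial and takes place at the ablation.
2. **Rhythm.** Bipolar voltage and conduction velocity depend on whether the atrium is in AF or sinus rhythm when mapped. In a mixed population the rhythm can differ between the two maps. If more patients move from AF to sinus rhythm than the reverse, the average would look like atrial recovery. The Discussion itself expects that weight loss may reverse the AF phenotype in some patients.

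Visit-aware readings can be redone masked if the images and maps are kept. The rhythm at a completed map cannot be changed, and if it was not recorded it may not be recoverable.

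**Working it through.** **Inputs from the article.** 30 recruits and about 10% dropout (Justification of sample size): 30 × 0.9 = 27 pairs. Analysis by paired t with two-sided 95% intervals (Statistical analysis). The article gives no SD, effect size or rhythm distribution for CMR or mapping, so every shift below is an assumption, expressed in SDs of the paired difference, with a true change of zero.

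**The article's own precision figure.** The only one concerns adherence, 21 of 30. The exact (Clopper–Pearson) limits are Beta(0.025; 21, 10) = 0.506 and Beta(0.975; 22, 9) = 0.853. Times 30, these are 15.2 and 25.6, which agrees with the stated 15–25 after truncation. This point does not affect it.

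**Step 1: half-width of the interval for a mean paired change.** t(0.975, n−1)/√n.
- n = 27: 2.056/√27 = 0.396 SD.
- n = 30: 0.373 SD.

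**Step 2: constant favourable reading shift b.** The t statistic is noncentral with parameter b√n. The chance that the interval excludes zero favourably is 1 − F(t(0.975, n−1); n−1, b√n). For b = 0.4 and n = 27, b√n = 2.078 and the chance is 0.517.

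| Shift b (SD) | n = 27 | n = 30 |
|---|---|---|
| 0 (nominal) | 2.5% | 2.5% |
| 0.2 | 17% | 18% |
| 0.3 | 32% | 36% |
| 0.4 | 52% | 56% |
| 0.5 | 71% | 75% |

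A shift about equal to the half-width thus excludes zero in about half of trials, not in all of them.

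**Step 3: a few rhythm-discordant pairs, all in one direction.** Suppose 5 of 27 pairs each move by 2 SD.
- Mean shift: 5 × 2/27 = 0.37 SD.
- The shifts also add spread. Expected sample variance: 1 + (5 × 22/27) × 2²/26 = 1.63, so the SD is about 1.28 and the half-width about 0.396 × 1.28 ≈ 0.50 SD.
- The shift is therefore about 0.37/0.50 = 74% of the half-width. By simulation the interval excludes zero favourably in about 26% of trials.

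**Step 4: direction of rhythm mismatch.** Simulation, n = 27, AF assumed to lower the reading by 1 SD.

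| AF to sinus | Sinus to AF | False improvement | False worsening |
|---|---|---|---|
| 20% | 20% | 2.6% | 2.5% |
| 30% | 10% | 14% | 0.2% |
| 30% | 0% | 28% | 0.0% |
| 10% | 30% | 0.2% | 14% |

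With the AF effect varied from 0.5 to 2 SD, the 30%/0% case runs from 11% to 60%. Balanced mismatch leaves the error rate nominal and only adds noise; the reverse imbalance would hide an improvement.

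**The case against.** The strongest reply is that the article is silent rather than wrong. It condenses a fuller protocol, and reader masking, batch reading or rhythm at acquisition may be fixed there or in an imaging or mapping manual. Treatment being open-label does not settle whether an image reader sees dates. The outcomes are exploratory, carry no p-values and cannot change the feasibility decision.

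Much of this stands, and it rules out several stronger readings that a reader might infer:

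- *The CMR reader is unmasked and reads scans as they arrive.* The article does not say so. It only fails to state masking.
- *A different catheter is used at the second map.* One is named for baseline only, but the right atrium is to be restudied for comparison, and nothing points to a change.
- *Rhythm mismatch will produce false improvement.* That needs a net shift towards sinus rhythm. The Discussion makes such a shift plausible, but the documents give no rhythm distribution.
- *Rhythm biases the CMR measures too.* The documents give no mechanism for epicardial fat or scar, so the rhythm point is confined to mapping.

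What does not fall away is what the article itself fixes: a mapping operator who must know the visit, two maps with no common rhythm set, a mixed AF population, no control arm, and a paired comparison over all patients meant to speak to mechanism. The CMR and mapping sections specify scanner, contrast dose, imaging delay and catheter model, so a line on masking and rhythm would be at the same level of detail.

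**Conclusion.** The point holds in limited form. As described, the paired CMR and mapping changes could not be attributed to weight loss with confidence: visit-masked reading is not stated for either, and rhythm is not controlled or accounted for in the maps. A modest bias is enough to matter at this sample size. Under the assumed shifts, false improvement rises from 2.5% to about 52% (constant 0.4 SD reading shift) or about 26% (five of 27 pairs shifted by 2 SD in one direction). These figures show sensitivity; they do not estimate bias in this study, and neither the presence nor the direction of bias can be shown from the document. The feasibility criteria are unaffected. This is a cheap improvement to exploratory outcomes, not a flaw in the feasibility design.

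**What to change.** 1. **CMR.** For the research measurements, strip date and visit labels, shuffle all scans, and have the same cardiologist contour and render them in one batch after the last ablation. Clinical reports continue unchanged. If the full protocol already provides for this, say so.
2. **Mapping.** Export the right atrial maps and analyse voltage and conduction velocity offline, masked in the same way. This masks the analysis only; acquisition cannot be masked.
3. **Recording.** Record rhythm and catheter at each mapping study, and tabulate rhythm at the first against the second map.
4. **Analysis.** Keep all pairs as the main comparison and add a sensitivity analysis in rhythm-concordant pairs. Rhythm at the second map is a post-treatment variable that weight loss might itself alter, so selecting on it can introduce its own bias; that is why it should not lead, and the report should say so.

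**Cost.** Later research readouts and some file handling by a coordinator. The reader, scans and procedures stay the same. The sensitivity analysis will use fewer pairs and be less precise.

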#### Biomarkers

Blood samples will be collected in QEHB at baseline and before ablation. The samples will be transported to the Institute of Cardiovascular Sciences at the University of Birmingham at room temperature for testing and storage. Samples will be stored in − 80 °C freezers of Human Biomaterials Resource Centre (HBRC) of University of Birmingham. HBRC has a licence from Human Tissue Authority. FGF-23 will be tested by using Olink® Target 96 CVD II panel. BMP-10 will be tested by using the enzyme-linked immunosorbent assay (ELISA).

#### Electroanatomic mapping in the right atrium

Electroanatomic mapping of the right atrium will be performed at baseline before treatment and then restudied at the time of ablation to allow comparisons of datasets. The reason for choosing right atrial mapping over the left atrium is to reduce the risks involved in crossing the atrial septum in study participants. In our study, right atrial bipolar voltage will be measured using a high-density mapping catheter (HD-Grid, Abbott) at baseline, and bi-atrial mapping will be performed at the time of ablation. The RA mapping will be performed by an experienced electrophysiologist ([name]).

#### Patient-reported outcome measures

The AFEQT is a validated patient-reported outcome measure designed specifically for AF-related symptoms [29]. It is a self-administered questionnaire which can be completed with 5–10 min. It is composed of 18 questions grouped into 3 functional subscales of symptoms, daily activities, and treatment concern. The score ranges from 0 (complete disability) to 100 (no disability). This will be measured at baseline, at the time of ablation, and at the end of study.

### Timeline and timing

The timeline of this feasibility study (Table 1) is designed to follow as closely as possible to the current NHS ablation pathway to minimize loss of follow-up and missing data. As the data collecting for the project is less likely to change within days, the investigators accept the window of 1 week for data collection point. This will help the researchers and the participants to reduce missing data as low as possible.

**Table 1 Tab1:** Schedule of events

**Time point**	**Study period**						
	**Enrolment**	**Post enrolment**					
	**-4 weeks**	**Baseline**	**13th week**	**26th week**	**39th week**	**52nd week**	**65th week**
**Enrolment**							
**Screening**	√						
**Informed consent**	√						
**Medical history**	√						
**Kardia provision**	√						
**Intervention**							
**Liraglutide**		Daily injections					
**Assessments**							
**BMI check**		√	√				√
**Blood tests**		√	√				
**CMR**		√	√				
**Right atrial mapping**		√	√				
**AF ablation**			√				
**Review on Kardia recordings**				√	√	√	√
**AFEQT**		√	√				√

### Statistical analysis

Descriptive statistics will be used to summarize demographics and medical histories. The number of patients recruited over 52 weeks will be reported as a percentage of those eligible. The adherence to the medication will be reported as a proportion of patients who tolerate a total cumulative dose of 657 mg of liraglutide or more over 52-week follow-up period. The cumulative dose of liraglutide will be calculated for each participant, and mean and standard deviation for all participants will be reported. The percentage of change in weight from baseline to the end of follow-up will be calculated for each participant, and the proportion of participants who lost weight ≥ 5% and < 5% will be reported. 

For the secondary outcome measures, descriptive statistics according to the data type will be used to report at each predefined time point (baseline, before ablation, and end of follow-up). Paired *t*-test will be used to compare the changes for continuous variables such as changes in CMR measurements, biomarkers, and electroanatomic data to determine potential mechanistic changes in relation to weight loss. As this is a feasibility study, the analysis will be reported as point estimates and corresponding 95% confidence intervals to provide precision of estimates, and no *p*-values will be reported. A Kaplan–Meier curve will be constructed for time to recurrence of AF at 1 year following ablation. This will be performed in preparation for the calculation of sample size with appropriate power for the future clinical trial based on a time-to-event superiority analysis.

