**Methods:**

The study is an open-label, uncontrolled, prospective single-centre feasibility study of daily liraglutide injections in the treatment of obese patients for at least 13 weeks before and 52 weeks after AF ablation. Adult patients with symptomatic AF whose body mass index ≥ 30 will be recruited from those planning to undergo ablation. Feasibility will be determined based on the recruitment rate, adherence to the medication, and the amount of weight loss achieved over the study period. Exploratory outcomes include changes in atrial structure, function, and fibrosis with weight loss evaluated by cardiac magnetic resonance imaging, electroanatomic mapping, and patient-reported outcome measure.

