### Aims and objectives

The primary aim of this feasibility study is to determine whether liraglutide injected 3 mg once daily for 13 weeks before first-time AF ablation and continued for 52 weeks after ablation is a feasible method of reducing the recurrence and burden of AF (reported as percentage of total recordings) detected by Kardia portable electrocardiogram (ECG) recordings (at least twice a day and according to symptom-triggered recordings) after catheter ablation in patients with paroxysmal or persistent AF and body mass index above 30. In our centre (Queen Elizabeth Hospital, Birmingham, QEHB), the usual waiting time for patients for their first-time ablation is at least 12 weeks. A shorter waiting time is unusual in the United Kingdom (UK), and a longer waiting time needs to be avoided, as delay increases risk of AF recurrence.

Feasibility (the primary objectives) of the study will be determined by the measurement of the following:The number of participants recruited as a proportion of those eligible for the study over the recruitment periodThe proportion of participants adherent to liraglutide until the end of 52 weeks follow-up after ablationThe percentage of weight loss (from recruitment) achieved at the time of ablation and the end of follow-up period after ablation.

Exploratory outcomes will also be determined as follows:The proportion of participants adherent to Kardia recording requirements (at least twice daily recordings over 52 weeks)The time-to-first recurrence of AF (> 30 s) beyond 12-week blanking period post ablationThe burden of AF (percentage of total observed time) beyond 12-week blanking period post ablation in predefined periods (13th–26th weeks, 27th–39th weeks, and 40th–52nd weeks following ablation)Changes in cardiac MRI (CMR) measures from baseline to before ablation◦ Epicardial adiposity (volume measure in cm^3^)◦ Left atrial fibrosis (percentage of scar to total atrial volume rendered in CEMERGAPP by using late gadolinium-enhanced left atrial CMR images)Changes in fibroblast growth factor (FGF)-23 (pg/ml) and bone morphogenic protein (BMP)-10 (ng/ml) levels from baseline to before ablationChanges in electro-anatomic mapping data (right atrial bipolar voltage [mV] and conduction velocity [cm/s]), from baseline to before ablation

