### Feasibility outcome measures

The study will be considered feasible if as follows:Recruitment rate ≥ 50% (≥ 30 patients) of those eligible (56 patients per year), drop-out rate < 10%, and data completeness ≥ 90%Adherence to medication rate ≥ 70% in the participants at the end of study [23]. Adherence will be measured by the proportion of patients who tolerate total cumulative dose of 657 mg and more of liraglutide at 1 year (minimal maintenance dose of 1.8 mg over 365 days).Weigh loss at least 5% from baseline in ≥ 60% participants at the end of study [23, 27]. Body mass change in kilograms and BMI between the baseline, at ablation, and last days of treatment with liraglutide (± 7 days) will be measured using a single set of calibrated scales using a standardized protocol.

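### The paired t-test on the CMR, biomarker and mapping data is given the purpose of relating changes to weight loss, but it uses no weight data and estimates only the mean change to ablation

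*Protocol article*

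**What the plan says.** In the Statistical analysis section, a paired t-test "will be used to compare the changes for continuous variables such as changes in CMR measurements, biomarkers, and electroanatomic data". The same sentence gives the purpose: "to determine potential mechanistic changes in relation to weight loss". The section also plans that "descriptive statistics according to the data type will be used to report at each predefined time point", and that results will be given as estimates with 95% confidence intervals and without p-values.

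The Methods paragraph of the abstract frames the aim similarly: "Exploratory outcomes include changes in atrial structure, function, and fibrosis with weight loss".

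Aims and objectives is narrower. The CMR item reads "Changes in cardiac MRI (CMR) measures from baseline to before ablation", and the biomarker and mapping items cover the same interval. None of the three mentions weight.

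On design, "This is an open-label, uncontrolled, prospective, single-centre feasibility study of liraglutide". On weight, Feasibility outcome measures plans to measure "Body mass change in kilograms and BMI between the baseline, at ablation, and last days of treatment with liraglutide".

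**The concern.** The sentence that names the method also names a purpose the method cannot serve. A question about how atrial or biomarker changes relate to weight loss needs each participant's weight change in the analysis. A paired t-test treats alike a participant who lost no weight and one who lost 10%.

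What is at stake is interpretation. The Discussion hopes that knowledge of reversibility, biomarker profiles and imaging will help select patients for ablation and time the procedure. If the mean change is the only inferential result, nothing in the stated analysis separates a change that tracks weight loss from one that merely happened during the same weeks.

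**Working it through.** **1. What the test estimates.** For participant i, let d_i be the value before ablation minus the value at baseline. The paired t-test is a one-sample analysis of d: the estimate is mean(d), with 95% CI mean(d) ± t(0.975, n-1) × SD(d)/√n. Weight change w_i appears nowhere, so reassigning the w values among participants leaves the result unchanged.

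A simulated illustration with assumed values (n = 27, weight loss with mean 6 and SD 4, d = -0.5w plus noise with SD 1.5):

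| | Mean change (95% CI) | Correlation of d with w |
|---|---|---|
| Weight loss as generated | -2.86 (-3.77 to -1.95) | -0.82 |
| Weight loss permuted among participants | -2.86 (-3.77 to -1.95) | -0.06 |

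The paired result is the same whether the relation is strong or nearly absent.

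**2. Whether another stated analysis fills the gap.** The descriptive statistics by time point do not use weight change either. The split at 5% weight loss is reported only as a proportion, from baseline to the end of follow-up, and is not linked to the CMR, biomarker or mapping measures.

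**3. Whether weight loss may vary enough to matter.** Feasibility outcome measures requires at least 5% loss in at least 60% of participants at the end of study. For 30 participants that is 0.60 × 30 = 18, so up to 12 could lose less than 5% and the criterion would still be met. That threshold applies at the end of study, not at ablation, but it shows that the plan itself allows for wide variation.

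**4. Whether the data exist.** Table 1 (Timeline and timing) schedules BMI, blood tests, CMR and right atrial mapping at both baseline and week 13. Weight change over the same interval is therefore available.

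**5. What a relation could show.** The plan gives no precision figure for these outcomes. Its one computed interval, for 21 of 30 adherent, is 50.6% to 85.3% by the exact method, or 15.2 to 25.6 participants. That agrees closely with the stated 15–25 and has no bearing on this point.

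Justification of sample size gives 30 recruits and about 10% dropout: 30 × 0.9 = 27 pairs, assuming every remaining participant has both measurements. The plan gives no correlation, so r is assumed over a range. The interval is tanh(atanh(r) ± 1.96/√(n-3)). At n = 27, 1.96/√24 = 0.400; at n = 30, 1.96/√27 = 0.377.

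| Assumed r | 95% CI, n = 27 | 95% CI, n = 30 |
|---|---|---|
| 0 | -0.38 to 0.38 | -0.36 to 0.36 |
| 0.3 | -0.09 to 0.61 | -0.07 to 0.60 |
| 0.5 | 0.15 to 0.74 | 0.17 to 0.73 |

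For comparison, the paired mean change has a 95% CI half-width of 0.40 SD of the change at n = 27 and 0.37 SD at n = 30. The correlation serves here as a unit-free guide to the precision of a slope. Adjusting for the baseline value would alter it somewhat.

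**The case against.** The strongest reply is that the outcome list under Aims and objectives governs. It defines these outcomes as plain changes from baseline to before ablation, and a paired mean change with a confidence interval is the natural estimate of that. The weight-loss wording could then mean only changes during the weight-loss period, and association models for exploratory outcomes are ordinary SAP content. Much of this stands: the paired analysis is right for the listed outcome, and rewording alone would cure the mismatch. It does not remove the point, because the article itself fixes a method and attaches to it a purpose that the method cannot serve. That is not a detail left to an unseen document.

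Some stronger readings are tempting but not supported:

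- *The paired t-test is the only analysis planned.* Descriptive statistics are also planned, although they do not link change to weight.
- *The plan will present a mean shift as a weight-loss effect.* Nothing commits to that. The text speaks of potential changes, omits p-values and discloses the uncontrolled design.
- *Regression to the mean is a leading explanation.* Inclusion depends on BMI, AF type and symptoms, not on the CMR, biomarker or mapping values, so this is a weak charge.
- *A gradient with weight loss is the only within-study evidence on mechanism, and it would settle the matter.* Cumulative liraglutide dose is also calculated per participant and offers another gradient. Weight loss may itself follow dose, adherence and uptake of lifestyle advice, so the slope is confounded too.
- *The slope would be informative.* That depends on the assumed r. At r = 0.3 the interval includes zero.

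**Conclusion.** The mismatch is real and of minor severity. The stated test answers change from baseline to before ablation, not a relation with weight loss. With no control arm, the mean change cannot be attributed to weight loss rather than to elapsed time, the lifestyle advice offered to all participants (Other aspects of care), rhythm at measurement or a drug effect independent of weight.

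A reader might infer that the feasibility conclusions are undermined. They are not: the criteria on recruitment, dropout, data completeness, adherence and weight loss do not use this analysis.

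That the test carries no information on the relation follows from its formula and needs no assumption. The precision figures rest on 27 complete pairs and on assumed correlations.

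**What to change.** Keep the paired mean change with its 95% CI. For each measure, add a linear regression of the baseline-to-ablation change on percentage weight change over the same interval, adjusted for the baseline value. Report the slope per 5% weight loss with 95% CI and no p-value, in line with the plan's reporting rule, and label it exploratory and non-causal.

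If the sponsor prefers not to add these models, reword the abstract's Methods paragraph and the Statistical analysis section to claim only change over the pre-ablation period.

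The first option costs a sentence in the analysis plan and about six models (epicardial adiposity, left atrial fibrosis, FGF-23, BMP-10, bipolar voltage, conduction velocity), with no new data. Its downside is about six imprecise estimates that could be over-read, so the confidence intervals and the non-causal label should accompany each one. The second option costs only the rewording.
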